## Abstract

**Objective:**

To evaluate the effectiveness of the Welch Allyn Connex^®^
Spot Monitor/Hillrom Connecta™ solution in activating the rapid
response team in a timely manner compared to manual activation.

**Methods:**

The Hillrom study is a single-center, open-label, superiority,
cluster-randomized, parallel-group (1:1 allocation ratio) clinical trial
that will be conducted in a tertiary hospital. Two sets of three wards with
28 beds will be included (one as the intervention cluster and the other as
the control). The wards will be randomly assigned to use the Welch Allyn
Connex^®^ Spot Monitor/Hillrom Connecta™
automated solution (intervention cluster) or to maintain the usual routine
(control cluster) regarding rapid response team activation. The primary
outcome will be the absolute number of episodes of rapid response team
triggering in an appropriate time; as secondary outcomes, clinical features
(mortality, cardiac arrest, need for intensive care unit admission and
duration of hospitalization) will be assessed according to clusters in an
exploratory way. A sample size of 216 rapid response team activations was
estimated to identify a possible difference between the groups. The protocol
has been approved by the institutional Research Ethics Committee.

**Expected results:**

The Welch Allyn Connex^®^ Spot Monitor/Hillrom
Connecta™ automated solution is expected to be more effective in
triggering the nurse call system to activate the rapid response team in a
timely and adequate manner compared to manual triggering (usual
practice).

**ClinicalTrials.gov:**

NCT04648579

## INTRODUCTION

Clinical decisions are based on data, which must be accurate and collected in a
timely manner.^(1)^ In hospital
settings, timely information is essential to trigger faster responses that can
ultimately determine the patient’s clinical outcome.^(2,3)^

Hospitalized individuals have their vital signs collected periodically with the aim
of preventing clinical deterioration, which could potentially reduce several
patient-centered outcomes.^(4)^ Vital
sign measurement practices vary greatly due to different risk profiles, clinical
complexity, and local protocols, among other factors. Data collection is often
manual, requiring computer entry of readout values or traditional pen and paper
workflows, which can result in errors and deviations in care.^(5)^ Manual recording can also delay
triggering specific protocols for the deteriorating patient, especially rapid
response teams (RRTs).

Despite having a crucial role in hospital care,^(6)^ data regarding the benefits of RRTs on clinical outcomes
are still controversial. Metanalyses from longitudinal studies (cohort and
interventional studies) have shown that RRT activation may lead to little or no
difference in hospital mortality, unplanned intensive care unit (ICU) admissions,
length of hospital stay or adverse events; in addition, the quality of evidence for
these outcomes was low or very low.^(7,8)^ Large and
well-designed clinical trials for evaluating the impact of RRTs properly triggered
on relevant features are still necessary.

Automated devices that can collect and exchange information without human
interference have been emerging as an interesting alternative to manual data
collection.^(9)^ These
devices can also trigger specific protocols, such as RRTs, without direct human
interference.^(4,9,10)^ However, despite the potential benefits of automated devices
over manual data collection,^(11,12)^ few clinical studies have been
performed to directly compare the two methods with respect to triggering the RRT and
hospital outcomes.^(7,9)^ Therefore, we designed a randomized
clinical trial to assess the hypothesis that the use of an automated vital signs
monitoring system associated with automatic activation of the RRT can result in an
increase in the number of faster and more effective activations in an appropriate
timely manner.

### Objectives

The primary objective of the study is to evaluate the effectiveness of the
solution Welch Allyn Connex^®^ Spot Monitor (CSM)/Hillrom
Connecta™ on triggering the RRT in an appropriate timely manner compared
to manual triggering.

The secondary objectives are to assess the following in an exploratory way:

- Clinical outcomes (mortality, cardiac arrest, need for ICU
hospitalization, and duration of hospitalization) among patients who had
the RRT automatically triggered by the Welch Allyn
Connex^®^ Spot Monitor (CSM)/Hillrom
Connecta™ compared to patients who had the RRT triggered
manually- The effects of the Welch Allyn Connex^®^ Spot Monitor
(CSM)/Hillrom Connecta™ on clinical outcomes (mortality, cardiac
arrest, need for ICU hospitalization, and duration of hospitalization)
compared between the intervention and the control wards

### Trial design

The Hillrom study (ClinicalTrials.gov Identifier: NCT04648579; 4th protocol
version [13/Apr/2021]) is a national, unicentric, cluster, parallel-group,
open-label, and superiority randomized clinical trial (allocation ratio
1:1).

## METHODS

### Study setting

The study will be conducted in a tertiary hospital located in the Southeast
region of Brazil. The HCor Research Institute (IP-HCor) will be responsible for
the protocol and coordination of the study. Data collection will commence after
compliance with all regulatory requirements, as well as training and adjustments
to the platforms and communication network necessary for automatic activation of
the RRT. There is no predetermined time for conducting the study; the admissions
of patients to the inpatient units will determine the study length. Wards with a
similar patient profile and a higher number of RRT activations compared to
regular wards will be selected and randomly assigned to use the Welch Allyn
Connex^®^ Spot Monitor (CSM)/Hillrom Connecta™
solution (Figure 1) or to maintain their
usual routine.

**Figure 1 f1:**
[figure not shown]
Connex^®^ Spot Monitor.

### Eligibility criteria

The inclusion criteria used to define the inpatient units (clusters) of the study
will be availability as defined by the heads of the hospital’s nursing area.
Patients admitted to the selected wards (all must be of medium complexity) who
triggered the RRT during the recruitment period will be included in the study;
patients with indications for blood pressure measurement via the lower limbs
(ankle) and those who are not candidates for either resuscitation or organ
support in the ICU will be excluded.

### Intervention

#### Description of the intervention

At the hospital where the study is conducted, current practice is based on
triggering the RRT if any of the following signs are identified in a given
patient-health care provider encounter:

- Decreased acute oxygen saturation to < 90%.- Hypoglycemia (defined as capillary blood glucose < 50mg/dL).- Change in respiratory rate (RR) to < 8rpm or > 28rpm.- Systolic blood pressure (SBP) < 90 or > 200mmHg.- Oliguria (defined by diuresis < 300mL in 24 hours).- Heart rate (HR) < 40bpm or > 130bpm.- Sepsis research, defined according to international
guidelines.^(13)^- Employee concern about the general status of the patient.- Acute neurological deficit.- Chest discomfort/pain.- Modified Early Warning Scores (MEWS) ≥ 5.^(14)^

The proposed intervention involves an automated vital signs documentation
system. This system consists of a portable medical device for measuring
vital signs (Welch Allyn Connex^®^ Spot Monitor (CSM),
Baxter International Inc, Deerfield, USA), which collects and analyzes the
data acquired at the bedside to be sent later to a remote data processing
point (Digital Control Station - DCS) using Hillrom Connecta™
software (Baxter International Inc, Deerfield, USA). Data on blood pressure,
HR, temperature, and oximetry are measured at the bedside by the equipment.
Other information, such as pain scores, RR and level of consciousness, are
manually collected by the nursing team and entered into the Welch Allyn
Connex^®^ Spot Monitor (CSM). After collecting all the
data, an institutionalized protocol for the Early Warning Score (EWS)
protocol already configured into the monitor calculates the final score for
patient deterioration risk based on the hospital criteria. All results are
automatically stored and transferred to the DCS, and they are sent to the
Hillrom Connecta™ software platform. The vital signs and the final
EWS can be visualized through a panel at the nurses’ station.

In addition, if at least one of the criteria for activating the RRT is
identified, the Hillrom Connect™ solution triggers the nurse call
system that automatically activates the RRT.

In the control wards, the usual practice will be maintained, which comprises
entering data into an Excel^®^ spreadsheet and maintaining
the frequency of monitoring/measurements according to the MEWS. The same
criteria for activating the RRT will be used; if any are identified by the
health professional, they will trigger the RRT manually at the bedside. The
RRT has up to 5 minutes to attend the patient.

#### Criteria for discontinuing or modifying the intervention

Considering that the interventions proposed in this study will be applied on
the wards and not directly on the patients, who will receive all care in a
standardized way regardless of the inpatient unit to which they are
admitted, there is no provision for discontinuity or modification of the
intervention.

#### Strategies to improve adherence to the intervention

All professionals involved in the research will be trained in this protocol
and in the use of the Welch Allyn Connex^®^ Spot Monitor
(CSM) and Hillrom Connecta™. The IP-HCor investigators will contact
the care team on a weekly basis to resolve doubts about the protocol and
handling of the equipment. Retraining will be carried out as requested by
the care team or upon identification of frequent failures by the
investigators.

#### Outcomes

The primary outcome of the study will be the absolute number of episodes of
RRT triggering in a timely manner, defined by any triggering that occurred
in the units randomized to the study and for which the patient had critheria
within a 24-hour window. Appropriate time will be considered if the RRT
appears at the bedside within 5 minutes after the yellow code is triggered
by a health professional. The triggering time as well as the arrival time
are recorded by the care team on a specific form attached to the patient’s
medical record.

The identification of whether the yellow codes were activated properly will
be verified by a care team not participating in the study. This verification
will be carried out by checking the codes identified by a specific platform
provided by the company *Eritel Telecomunicações
Ltda.* (Eritel Telecommunications Limited)
*versus* the codes recorded in the medical record. If the
platform originates a code, but it was not confirmed/effective according to
the nursing team’s verification, it will be considered false triggering
(improper triggering).

The following secondary outcomes will be considered: mortality rates, cardiac
arrest, need for ICU hospitalization (defined according to institutional
protocols and trained staff) and duration of hospitalization during the
study.

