#### Timeline

All RRT activations that occur in randomized units (intervention and control)
will be recorded until the necessary number estimated in the sample
calculation is obtained. The medical records of the respective patients will
be obtained for evaluation and recording of data referring to primary and
secondary outcomes (Figure 2). The
general protocol schedule is described in table 1.

**Table 1 t1:** General study schedule

	Study period			
	**Prerecruitment**	**Recruitment**	**Post-recruitment**	**Close-out**
Timepoint	November 2019 - March 2021	April - September 2021	October 2021 - March 2022	April - August 2022
Study design	X			
Submission and approval of the study protocol by the REC	X			
Team training	X			
Recruitment - Intervention group and control group		X		
Input of all data in the database (REDCap system)			X	
Data analysis				X
Submission of results				X

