#### Sample size calculation

A set of three wards with 28 beds will be considered the intervention cluster
(with the Welch Allyn Connex^®^ Spot Monitor (CSM)/Hillrom
Connecta™ solution), and a set of three wards with 28 beds will be
considered the control cluster. The average monthly number of episodes of
RRT triggering in the six selected wards is 12, of which it is estimated
that approximately 70% are triggered in a timely manner. For an absolute
increase of 18% in the proportion of timely RRT triggering (88%) in the
intervention group, with a test power of 90% and a significance level of 5%,
we estimated a sample size of 216 RRT activations.

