#### Statistical analysis

The demographic and clinical characteristics of the sample will be summarized
according to the groups in absolute and relative frequencies for the
categorical variables; continuous variables will be presented by position
statistics (mean, median) and scale (standard deviation and interquartile
ranges).

The analysis for the primary outcome (events that trigger the RRT in a timely
manner) will be conducted with a logistic regression model considering
binomial distribution from generalized estimation equations, considering a
uniform work correlation matrix between patients of the same ward adjusted
for the baseline number of episodes of RRT triggering in an appropriate
timely manner. Other outcomes will be compared using a similar methodology
considering the response distribution that best fits the data. All results
will be presented considering measures of effect with respective 95%
confidence intervals.

Sensitivity analyses for the primary outcome considering time series
assessments and time of RRT activation (weekday *versus*
weekend; night *versus* day shifts) will be performed
comparing treatment groups. The results will be presented in graphs with
monthly indicators.

It is not expected that there will be a large amount of missing data.
However, if some of the primary and secondary outcomes are missing, the
missing data rate will be reported by group, and the values will be imputed
by chained equation multiple imputation methods using the mice package with
sample base characteristics.

All analyses will be performed with statistical R software 4.0.2 (R Core
Team, Vienna, Austria, 2020). Interim analyses or the participation of a
Data and Safety Monitoring Committee (DSMC) are not foreseen in the
protocol.

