#### DISCUSSION AND TRIAL STATUS

The measurement of vital signs is a fundamental component of patient
assessment, providing the basis for clinical decision-making from treatment
to hospital discharge. Therefore, these data must be accurate and quickly
accessible so that safe decisions can be made.^(16)^ In an American university hospital, error
rates were evaluated for electronic documentation of vital signs compared to
manual records on paper. As a result, it was found that the use of the
system reduced vital signs recording errors by more than half compared to
traditional manual documentation (error rates: 4.4% and 10%,
respectively).^(17)^
In addition, the implementation of the automated clinical documentation
system allowed the nursing team to increase the time spent on direct patient
care.^(18)^

Despite the lack of consistent evidence showing the effectiveness of RRT
systems on clinical outcomes, they have been implemented at hospitals
worldwide.^(6)^ After
the introduction of RRTs in a large Brazilian nonprofit hospital, a
significant reduction in waiting time for ICU beds among inpatients who
could not be admitted immediately after indication was determined, as well
as an increase in the recognition of palliative care patients; however, no
difference in hospital mortality was detected.^(19)^ Similar results were observed after the
implementation of RRTs in a Brazilian university hospital, where a reduction
was observed in in-hospital cardiac arrest but not in hospital
mortality.^(20)^

Electronic systems for automated notification of vital signs may contribute
to reducing call delays, one of the most important barriers to successful
implementation of RRTs^(21)^
associated with increased hospital mortality.^(22)^ In addition, they may increase the number
of RRT activations. In a before-and-after study conducted in wards in the
UK, the use of an electronic vital signs monitoring solution increased RRT
activations from 405 to 524 (p = 0.001). In addition, a decrease in overall
mortality and in the number of cardiac arrests was observed during the
protocol intervention period.^(23)^ However, it is noteworthy that before-and-after
studies are susceptible to a number of methodological biases compared to
randomized trials, which can ultimately invalidate the results or impair the
clinical significance of the study.^(24)^

The Hillrom study aims to evaluate, through a cluster randomized clinical

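### The primary outcome is declared as a count of timely activations, but the sample size and the primary model are for the proportion of activations that are timely

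*Protocol article*

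**What the plan says.** **The outcome is a count.** The Outcomes section reads "The primary outcome of the study will be the absolute number of episodes of" timely RRT triggering, and the Abstract and the Discussion and trial status section repeat the absolute number. The Introduction hypothesises an "increase in the number of faster and more effective activations in an appropriate" time.

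**The sample size is for a proportion.** The Sample size calculation section takes it "that approximately 70% are triggered in a timely manner" and plans for an absolute "increase of 18% in the proportion of timely RRT triggering (88%) in the" intervention group. With 90% power and a 5% significance level it arrives at 216 activations.

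**The model is for a proportion.** In the Statistical analysis section, the primary outcome (events triggering the RRT in a timely "manner) will be conducted with a logistic regression model considering" a binomial distribution, fitted by GEE with a uniform working correlation within ward. It is adjusted for the baseline number of timely episodes. No exposure term is named.

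**Accrual is by activations.** The Timeline section says that activations in the randomised units "will be recorded until the necessary number estimated in the sample" calculation is reached. The 1:1 ratio applies to wards. Nothing fixes how the activations divide between arms.

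**Volume may change.** The Discussion and trial status section says electronic notification may increase RRT activations and cites a before-and-after study in which they went from 405 to 524.

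**The concern.** A logistic model for activations estimates the odds that an activation is timely, given that one took place. It says nothing about how many timely activations a ward had, which is what the outcome definition and the hypothesis ask about.

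If both arms were bound to contribute the same number of activations, the two measures would always point the same way. They are not bound to do so, and the device acts on the very step that creates an activation. Extra calls raise the count of timely activations unless timeliness falls enough to offset them, whereas the proportion can move either way.

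The two measures also have different weaknesses:

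- The proportion is conditioned on activations, which arise after randomisation and may be changed by the device. Under the Eligibility criteria only patients who triggered the RRT enter, so a patient who met the criteria but was never called is not seen.
- The count has no admissions or bed-occupancy term in the planned model.

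At stake is which claim the trial can make: more timely activations, or a larger share of activations that are timely.

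**Working it through.** **1. Reproduce the 216.** Inputs from the Sample size calculation section: p₁ = 0.70, p₂ = 0.88, power 90%, 5% significance. Two-sided testing and equal arms are assumed. For two independent proportions with pooled variance and no continuity correction:

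n per arm = [1.960·√(2·0.79·0.21) + 1.282·√(0.70·0.30 + 0.88·0.12)]² / 0.18²
= (1.129 + 0.720)² / 0.0324 ≈ 105.5, rounded up to 106, so 212 in total.

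This is within 2% of 216, and 108 per arm gives 90.7% power. The stated size is that of a comparison of proportions, without allowance for clustering.

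**2. When the two measures disagree.** Let r be the intervention-to-control ratio of activations, and p_I and p_C the timely proportions. The count ratio is r·p_I/p_C. The odds ratio depends only on p_I and p_C. At r = 1 the two agree in direction. For r > 1 they disagree whenever p_C/r < p_I < p_C.

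**3. Illustration with the cited volume ratio.** Assumptions: r = 524/405 = 1.294, p_C = 0.70, and 216 activations in total.

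- Control activations: 216/2.294 = 94.2. Intervention: 121.8.
- Control timely: 0.70 × 94.2 = 65.9.
- Lower limit for a higher count in the intervention arm: 0.70/1.294 = 54.1%.

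| Assumed intervention timeliness | Timely, control v intervention | Count change | Odds ratio |
|---|---|---|---|
| 70% | 66 v 85 | +29% | 1.00 |
| 60% | 66 v 73 | +11% | (0.60/0.40)/(0.70/0.30) = 0.64 |
| 54.1% | 66 v 66 | 0% | (0.541/0.459)/(0.70/0.30) = 0.51 |

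The reverse pattern needs fewer activations in the intervention arm. For example, 108 control activations at 70% give 75.6 timely, and 80 intervention activations at 88% give 70.4. The count falls by 7% while the proportion rises by 18 points.

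**4. Are these differences significant?** Clustering is ignored:

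- 66 v 85: z ≈ 19/√151 = 1.55, p ≈ 0.12.
- 66 v 73: z ≈ 7/√139 = 0.59, p ≈ 0.55.
- Odds ratio 0.64: ln 0.643 = −0.442, SE = √(1/65.9 + 1/28.2 + 1/73.1 + 1/48.7) = 0.291, z ≈ −1.52, p ≈ 0.13.

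None reaches 5%.

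**5. Power for the declared count.** Assumptions: Poisson counts, equal exposure, no clustering, two-sided 5%.

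- Equal volume: rate ratio 0.88/0.70 = 1.257, timely 75.6 v 95.0. SE = √(1/75.6 + 1/95.0) = 0.154, so power = Φ(0.229/0.154 − 1.96) ≈ 32%.
- For 90% power at equal volume: (1.960 + 1.282)²·(1 + 1/1.257)/0.229² ≈ 360 timely control episodes, which is 360/0.70 ≈ 515 control activations and about 1,030 in total.
- If volume also rises by 1.294: rate ratio 1.257 × 1.294 = 1.63, and the same formula gives about 72 timely control episodes, or about 235 activations in total.

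The size needed for the declared outcome therefore depends on a volume assumption that the article does not make.

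**The case against.** The strongest defence is that the sample size and the model already agree with each other, so only the label is out of step. The article also calls the study exploratory, calls the sample size preliminary, and says the outcome was chosen with that in mind. This lowers the stakes and points to the smallest correction. It does not say which quantity is primary, and the article elsewhere describes a superiority trial. A separate analysis plan could not remove the conflict either, because all three statements stand in this document. Adjusting for the baseline number of timely episodes does not supply an exposure term.

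Some stronger readings are tempting but not supported:

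- *Neither measure has a valid denominator.* The proportion has one, namely activations. The fair criticism is that the device may change it. For the count, both arms are described alike (three wards with 28 beds) and recruit concurrently, so nominal exposure is roughly similar. Stopping at a fixed overall total closes both arms together and does not itself invalidate the comparison.
- *The article expects more activations.* It says only that they may increase. The 405-to-524 figure comes from a design that the article itself calls open to bias, so 1.29 is one scenario. The 60% timeliness has no source in the article and is purely an assumption.

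**Conclusion.** The inconsistency stands. The declared primary outcome is a count, while the trial is sized and analysed for a proportion, so the declared outcome is neither powered nor tested. The mismatch can be seen from the text alone and needs no assumption.

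Its possible size does rest on assumptions. With a volume ratio of 1.29 and 70% timeliness in control, any intervention timeliness between about 54% and 70% gives a higher count together with an odds ratio below 1.

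A reader might infer that the same data could be declared a success on one definition and a failure on the other. The worked examples do not show that. Point estimates diverge or reverse, but none is significant on either scale, and positive within-ward correlation would generally weaken them further. What is established is that the conclusion has no single defined quantity behind it.

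**What to change.** Before database lock:

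1. Name the proportion of confirmed activations that are timely as the primary outcome in the Abstract, Introduction hypothesis, Outcomes and Discussion, and remove the absolute number. This matches the existing sample size and model. The word confirmed also settles that false triggers stay out of the denominator.
2. Report beside it, by arm, total and timely activations per ward admission, as a secondary count-model analysis with a log-admissions offset. The Cluster-level data section already promises admissions to the selected wards during the study. Ward patient-days are not promised, so admissions are the readier exposure.
3. Limit the primary conclusion to timeliness given activation.

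The cost is mainly wording plus one secondary analysis. The real downside is that the headline claim narrows from the number of timely activations to the proportion that are timely.

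If the sponsor prefers to keep the count as primary, it needs a count model with an exposure offset, and the 90% power statement must be withdrawn (about 32% with 216 activations at equal volume, under Poisson counts and no clustering). That route is not cheap. Recruitment closed in September 2021, so accrual cannot grow without reopening it, and replacing the primary model after an open-label recruitment period would itself need justifying.

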#### Individual-level data

Baseline variables (at the time of hospitalization): age, gender,
type of hospitalization, Charlson morbidity score.^(15)^Outcomes (during hospitalization): in-hospital mortality, duration of
hospitalization, need for ICU hospitalization, cardiac arrest, and
selected relevant clinical events (stroke, myocardial infarction,
and sepsis).

The nursing teams that work in the selected units will receive training prior
to the beginning of the clinical trial. During the training, the study
protocol and the Good Clinical Practices (GCP) guide will be presented.
Hands-on training in the handling of the device by a device specialist will
be provided to the care team at selected facilities that will use both Welch
Allyn Connex^®^ Spot Monitor (CSM) and Hillrom
Connecta™ devices.

Data will be collected through the physical records of patients who require
the triggering of the RRT code in the selected wards during the recruitment
period. These data will comprise age, sex, date of admission, reason for
hospital admission, diagnostic class of hospital admission, previous
comorbidities, date and time of yellow code triggering, physiological data
in the last 24 hours (HR, RR, SBP, diastolic blood pressure, temperature,
oxygen saturation, level of consciousness, capillary blood glucose [if
available], chest discomfort/pain, leukocytes [if available], presence of
sepsis, diuresis, poor general condition of the patient) collected at four
time points, problems related to yellow code triggering, clinical outcomes,
and hospital discharge/transfer/death. The frequency of vital signals
obtained will be the same between groups (four measurements 24/7 in each
group).

The analysis of the physical record and the input of data for the electronic
case report form (CRF) will be carried out by HCor professionals, who will
be previously trained in relation to the data capture system.

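### The primary outcome starts its clock at the yellow code, so it measures team attendance after the call and not the timeliness of triggering that the trial sets out to test

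*Protocol article*

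**What the plan says.** **Outcome (Outcomes).** The primary outcome is the absolute number of timely RRT triggering episodes. An episode qualifies if it occurred in a randomized unit and is one "for which the patient had critheria within a 24-hour window". It is in appropriate time if the team "appears at the bedside within 5 minutes after the yellow code is triggered" by a health professional. On timing data the section says "The triggering time as well as the arrival time are recorded by the care team", on a form in the medical record. No other time enters the definition.

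**Question (Introduction, Objectives, Discussion).** The Introduction states the problem: "Manual recording can also delay triggering specific protocols for the deteriorating patient". Its hypothesis is an "increase in the number of faster and more effective activations in an appropriate" time. The primary objective is about triggering the team, not about its arrival. The Discussion says automated notification may contribute "to reducing call delays, one of the most important barriers to successful" implementation of such teams.

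**Device (Description of the intervention).** If a criterion is identified, the solution triggers the nurse call system, which activates the RRT automatically. In control wards staff call manually at the bedside. The team then has up to 5 minutes to attend, the same limit that the outcome uses.

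**Data (Individual-level data).** Record abstraction covers "comorbidities, date and time of yellow code triggering, physiological data" from the last 24 hours at four time points. Measurement frequency is stated to be the same in both groups.

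**The concern.** The device is described as acting between the abnormal reading and the call. The outcome times the interval between the call and the team's arrival. The only tie to the abnormal reading is the 24-hour window, which decides which activations qualify. It neither measures nor limits how long the call took.

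Two hypothetical cases show the result. A call made 20 hours after the first qualifying reading and attended in 4 minutes scores as timely. An immediate automatic call attended in 6 minutes does not.

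What is at stake is the interpretation of the primary result. A null finding could arise even if the device shortened the delay from reading to call, and a positive finding could come from attendance speed alone. Neither would answer the stated objective, and the Discussion intends the result to lead to a multicenter study.

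A smaller defect sits in the same sentence. A code triggered by a health professional describes a manual call. Taken literally, it does not define the clock start for the automatic codes that are the normal route in the intervention wards.

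**Working it through.** **1. The intervals side by side**

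| Interval | Device action described? | In the outcome? |
|---|---|---|
| Criterion recorded to yellow code | Yes (Description of the intervention; rationale in Introduction and Discussion) | Only as a 24-hour qualifying window |
| Yellow code to team at bedside | None described; it is the team's own 5-minute standard | Yes, this is the clock |

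**2. The plan's own sample size.** Inputs from Sample size calculation: 70% and 88%, power 90%, significance level 5%, 216 activations. The 1:1 ratio is from Trial design. A two-sided test is assumed, and clustering is ignored.

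Pooled-variance formula, with p̄ = (0.70 + 0.88)/2 = 0.79:

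n per arm = [1.960·√(2·0.79·0.21) + 1.282·√(0.70·0.30 + 0.88·0.12)]² / 0.18²
= [1.960·0.5760 + 1.282·0.5618]² / 0.0324
= 1.849² / 0.0324 ≈ 105.5, so 106 per arm and 212 in total.

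This is within 2% of 216 (4/216 = 1.9%). The point therefore does not rest on a sample size error. It also shows that 216 treats the outcome as a proportion of activations, as does the logistic model in Statistical analysis.

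**3. What the proportion can register.** With 216/2 = 108 activations per arm, p1 = 0.70 and intervention rate p2:

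Power = Φ{[(p2 − p1)·√108 − 1.960·√(2p̄(1 − p̄))] / √(p1(1 − p1) + p2(1 − p2))}

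| Intervention rate of arrival within 5 minutes (assumed) | Difference | Chance of a significant result favouring the device |
|---|---|---|
| 70% (attendance speed unchanged) | 0 points | 2.5% |
| 75% | 5 points | 12.7% |
| 80% | 10 points | 39.6% |
| 85% | 15 points | 75.5% |
| 88% (planned) | 18 points | 90.7% |

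Criterion-to-call delay appears nowhere in this formula. For qualifying activations, the outcome moves only through code-to-bedside time. The 75% to 85% rows stand for an indirect gain in attendance speed, on which the document gives no data.

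**4. The count reading.** Outcomes and the Discussion also describe the outcome as an absolute number. The Discussion cites a before-and-after study in which activations rose from 405 to 524, a ratio of 524/405 = 1.29. If activations rose by that ratio and the same share were attended within 5 minutes, the count of timely episodes would rise by 29% and the proportion would not change. A count can thus respond to the device through extra calls, but it still contains no measure of delay.

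**5. What cannot be computed.** The document gives no criterion-to-call times in either arm, so no rate or power under a delay-based definition can be derived.

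**The case against.** The strongest reply has four parts.

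- **The outcome is a count.** Under the absolute-number wording the device can succeed by prompting more calls, so a zero effect is not inevitable. This stands. The zero applies only to the proportion reading in Sample size calculation and Statistical analysis, and only if attendance speed is equal.
- **The device might speed attendance.** The document does not describe the steps between a manual call and the team being alerted, so automatic activation could save time there. This also stands as a possibility. Equal attendance is an assumption, which is why step 3 shows a range.
- **The trial is exploratory and recruitment is complete.** The Discussion says both, and says the outcome was chosen with the exploratory design in mind. This argues against replacing the primary outcome now: an open-label trial would be switching after recruitment, and the 70%, 88% and 216 figures would no longer apply. It does not make the present measure answer the objective.
- **The clock-start wording is only loose.** The form records triggering and arrival times, platform codes are checked against the record, and the care team confirms all episodes. This largely stands. A reader might infer that the arms were actually timed from different events, but the document does not show that. It shows only wording that does not cover automatic codes.

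A reader might also infer that the outcome hides hours of earlier detection. The document does not support this. Measurement frequency is the same in both groups, readings are bedside spot measurements, and respiratory rate and level of consciousness are entered by hand. What the device can be expected to shorten is the time from reading to call, and the size of that delay is not given.

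**Conclusion.** The mismatch is real and lies in an explicitly stated definition, so it is not a detail left to a fuller document. The primary outcome measures attendance within 5 minutes of a code, while the objective concerns timely triggering.

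On the proportion reading, a shorter reading-to-call delay cannot move the result. With equal attendance speed in both arms, the expected difference is 0 points against the planned 18, and the chance of a significant result for the device is 2.5% against 90.7% at the planned effect. These figures assume a two-sided 5% pooled test, 108 activations per arm and no clustering. On the count reading extra calls could raise the outcome, but delay remains unmeasured.

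The documents do not support saying that the trial must show no effect, or that the primary outcome has to be replaced at this stage. They support adding a measure of triggering delay, repairing the clock wording, and limiting what is concluded from the 5-minute measure.

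**What to change.** Before any unblinded analysis:

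1. **Prespecify a key supplementary outcome.** In both arms, measure the delay from the first recorded vital-sign set in the previous 24 hours that met a listed RRT criterion to the yellow code, and likewise to the bedside. Analyse it as a time, or with a cut-off that the investigators set in advance. Date the addition and report it as made after recruitment.
2. **Reword the clock start.** Remove the attribution of the code to a health professional, and state one event and one source of time for automatic and manual codes alike.
3. **Relabel the present measure.** Call it RRT attendance within 5 minutes of a code. State that a null result on it will not be read as no effect on timely triggering.

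**Cost and limits.** Code time and 24-hour physiological data are already on the abstraction list, so the main work is wording plus some extra abstraction. Four limits need stating:

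- Individual-level data gives no clock time for each vital-sign set, so availability must be confirmed.
- Four readings in 24 hours date the criterion only to about 24/4 = 6 hours if evenly spaced.
- Criteria without a recorded time, such as staff concern, need a stated fallback and may cover many calls.
- Eligibility criteria include only patients for whom the RRT was triggered, so those who met a criterion and were never called are not captured.
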